### Sample size

Because there are no large-scale community-led randomised controlled trial interventions with reducing loneliness as a primary outcome, we had to estimate power based on the number of participants and maximum number potential covariates we will need to account for. Power calculations were calculated using PowerUp! [50]. Power was set at 0.80 and an Alpha threshold of 0.05. Estimated pre-post correlations for loneliness are between .35 and .83 [51, 52] and for a conservative estimate the lowest correlations for each outcome are used. Therefore, for a projected sample of 1500 participants per country and with up to 20 co-variates for the primary outcomes of loneliness, a minimum detectable effect size (MDES) for a trial effect is .14 in an intention-to-treat (ITT) analysis. Given recent recommendations that Cohen’s effect size benchmarks are too stringent to detect important effects in social and personality psychology [53, 54], we see an effect size of .14 being of small-medium size that is of some explanatory and practical use, even if only in the short-term and therefore clinically meaningful. Further, noting that the strength of an intervention is best evaluated in relation to outcomes it aims to achieve [55], we are guided by a meta-analysis of loneliness intervention trials that found a mean intervention effect size of − 0.198, but with much variability (95% CI: − 0.32, − 0.08; [56]). Thus, previous research has typically found small-medium effects on average for loneliness interventions and this study is sufficiently powered to detect effects of a comparable magnitude.

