### Implementation secondary outcomes

#### Feasibility

Feasibility will be the following: having a high retention rate (i.e., < 40% drop-out).

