### Recruitment and enrolment

We will recruit through a sample of Nextdoor users within each country using online promotions and, or an email to all users within each country database. The recruitment strategy will not be constrained to neighbourhood location or demographics in order to ensure that we recruit a diverse range of participants in order to generalise the data across the different Nextdoor communities. We will aim to recruit approximately 1500 community dwellers aged 18 to 90 years across each country (Australia, UK, USA), with an overall estimate of 4500 participants across three countries. These recruitment targets are feasible given the number of users active within each country (at least 500,000 users).

The external organisation Nextdoor will be responsible for recruitment of participants and will invite users within each country without specific parameters. This is to ensure we recruit all kinds of users, including those who are high and low users of the program, and those who are from low to high socio-economic status. Potential participants will respond to advertisements embedded in the Nextdoor website platform that they are already a member of. Nextdoor will recruit via email, push notifications (website and app). If an individual is interested in participating, they will be directed to a Qualtrics survey containing a participant information statement and consent form. This Qualtrics survey is only accessible by Swinburne University of Technology. In this survey, participants will provide online consent to take part in Nextdoor KIND Challenge. Following consent being obtained, participants will complete a baseline survey and will be randomised into the KIND Challenge condition or a waitlist condition.

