### Allocation and blinding

Simple randomization (1:1) will be used as the study is conducted entirely on online questionnaire software Qualtrics. Blinding is not possible in this RCT and there may be recruitment biases that may occur (e.g., those who choose to participate may already be more altruistic and more open to being engaged within research studies).

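### The detectable effect of .14 is computed on the full recruitment target of 1500 per country, with no allowance for attrition, although the protocol treats drop-out of up to 40% as feasible

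*Protocol article*

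**What the plan says.** The Sample size section fixes the error rates ("Power was set at 0.80 and an Alpha threshold of 0.05"), gives pre-post correlations for loneliness of .35 to .83, and takes the bottom of that range: "for a conservative estimate the lowest correlations for each outcome are used". It then states, "for a projected sample of 1500 participants per country and with up to 20 co-variates", that "a minimum detectable effect size (MDES) for a trial effect is .14 in an intention-to-treat (ITT) analysis". It calls an effect of that size clinically meaningful. It closes by comparing it with a meta-analytic mean of −0.198 and concluding that power is sufficient for effects of that order.

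The Recruitment and enrolment section uses the same number as the enrolment goal: "We will aim to recruit approximately 1500 community dwellers aged 18 to 90 years across each country". Randomisation follows the baseline survey. Neither section mentions loss to follow-up.

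Under Implementation secondary outcomes, feasibility is defined as "having a high retention rate (i.e., < 40% drop-out", and the descriptive criteria at the end of Secondary outcomes analysis repeat the 40% limit. No time point is attached to it. Statistical methods specifies a separate analysis for each country. Missing data plans a complete-case analysis below 5% missing and full information maximum likelihood (FIML) above that, if data are missing at random.

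**The concern.** A detectable effect depends on the number of people who supply the outcome, not on the number enrolled. Here the two are the same figure, so the stated .14 carries an unspoken assumption that everyone recruited returns a 4-week loneliness score. This is an unblinded trial run by online survey, and its own feasibility criterion tolerates losing up to two participants in five.

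The protocol puts weight on .14 by describing it as an effect of practical and clinical interest. If retention is moderate, a reader who relies on the sample-size statement will believe that each country's trial had 80% power for that effect when it had less. Because the countries are analysed separately, pooling does not make up the shortfall. The point concerns a number the article does state, so it is not a matter of detail left to a fuller document.

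**Working it through.** **Inputs**

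- Power .80 and alpha .05 (Sample size). Sidedness is not stated, so two-sided is assumed.
- N = 1500 per country (Sample size; the same figure in Recruitment and enrolment).
- g = 20 covariates: "with up to 20 co-variates for the primary outcomes of loneliness".
- Pre-post correlation r = .35, the lowest in the stated range, so R² = .35² = .1225.
- Allocation: "Simple randomization (1:1) will be used", so P = .5 and P(1 − P) = .25.

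**Formula** (individually randomised design, covariate-adjusted)

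MDES = (t₀.₉₇₅,df + t₀.₈₀,df) × √[(1 − R²) / (P(1 − P)N)], with df = N − g − 2.

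**Step 1: reproduce the protocol's figure.** At N = 1500, df = 1478 and the multiplier is 1.962 + 0.842 = 2.803. The standard error is √[.8775 / (.25 × 1500)] = .0484. MDES = 2.803 × .0484 = .136, which rounds to the stated .14.

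Variants at N = 1500:

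- R² = 0 gives .145 (.1448 before rounding, so also .14 to two decimals).
- Entering .35 directly as R² gives .117.
- r = .83 gives .081.
- A one-sided test with r = .35 gives .120.

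So the protocol's stated basis reproduces .14 with all 1500 contributing.

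**Step 2: the same formula with fewer outcomes, r = .35.** Power is from the noncentral t distribution.

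| Loss | Outcomes per country | MDES | Power for .14 | Power for .198 |
|---|---|---|---|---|
| 0% | 1500 | .136 | .82 | .98 |
| 10% | 1350 | .143 | .78 | .97 |
| 20% | 1200 | .152 | .73 | .96 |
| 30% | 1050 | .162 | .68 | .93 |
| 40% | 900 | .175 | .61 | .89 |

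The MDES still rounds to .14 down to about 1315 outcomes: 1 − 1315/1500 = 12% loss.

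**Step 3: sensitivity to the correlation.**

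- r = .50, 20% loss (1200): .140.
- r = .59, the midpoint of the range, 30% loss (1050): .140.
- r = .66, 40% loss (900): .140.
- r = .83, 40% loss (900): .104.
- r = 0, 40% loss (900): .187.

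**Step 4: does FIML recover the loss?** The primary model regresses the post-intervention score on group and baseline covariates. A participant with baseline data but no post-intervention score adds nothing to the estimate of the group coefficient in that model. FIML keeps such people in the likelihood and addresses bias under missing at random. It does not restore the precision their outcomes would have given.

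**The case against.** The strongest reply has four parts.

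*The calculation is right.* The sentence is conditional on a projected 1500, and .14 follows from the stated inputs. This stands. A reader might infer an arithmetic error, but there is none. The gap is an unstated assumption, and even that is inferred: the article nowhere says in words that all 1500 will give an outcome. The inference rests on the enrolment goal and the N in the calculation being identical, and on .14 reproducing at that N.

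*Forty per cent is a pass mark, not a forecast.* This also stands. A reader might infer that the protocol expects about 900 analysed per country. It does not say so. The limit has no time point and could refer to the one-month follow-up, whereas the primary comparison is at 4 weeks. The point does not depend on reaching the limit, however: 20% loss already brings power for .14 to .73.

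*The correlation is deliberately pessimistic.* True. At .50 or above, .14 survives 20% loss to within rounding. It would therefore be too strong to say that the design cannot detect .14 once people drop out. But the protocol chose .35 as its conservative basis, and on that basis the figure fails beyond about 12% loss. Pairing a cautious correlation with zero attrition is not a conservative statement overall.

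*The conclusion is unaffected, and a null result would be read from its confidence interval.* Largely true. The claim about effects near .198 holds even at 900 analysed, and nothing in the document proposes to treat non-significance as excluding .14. A reader might conclude that the trial is underpowered or must recruit more. The documents do not support that: N was a projected number from which power was estimated, not a requirement derived from a target effect.

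**Conclusion.** The concern holds in limited form. The .14 is correct for 1500 outcomes per country but is stated without the condition on which it depends, in a protocol that accepts substantial drop-out. On the protocol's own conservative basis, the detectable effect rises from .136 to .152 at 20% loss and .175 at 40%, and power for .14 falls from .82 to .73 and .61.

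These figures assume a two-sided .05 test, r = .35, 20 covariates that explain no variance beyond baseline loneliness, equal arms with equal loss, and no information on the group effect from people without a 4-week score. The correlation matters most: towards the upper end of the stated range, .14 remains detectable even at 40% loss.

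This calls for a correction to a stated design property. It does not undermine the trial, the analysis or the broader claim about effects near .198, for which power is about .89 at 900 analysed.

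**What to change.** Amend the Sample size section to say, in substance: *MDES .14 if all 1500 participants per country give a 4-week outcome; about .15 at 20% loss and .18 at 40% loss, with r = .35.* State that the test is two-sided, if it is, and add that the values are smaller at higher correlations (for example .104 at 40% loss with r = .83).

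Rest the claim of adequate power on the .198 benchmark, where it holds across the whole drop-out range the protocol accepts, and not on .14. It would also help to attach a time point to the 40% criterion, so that readers can tell whether it covers the primary outcome.

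The cost is one or two sentences and a less favourable headline figure. Recruitment, outcomes and analysis stay as they are.

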### Recruitment and enrolment

We will recruit through a sample of Nextdoor users within each country using online promotions and, or an email to all users within each country database. The recruitment strategy will not be constrained to neighbourhood location or demographics in order to ensure that we recruit a diverse range of participants in order to generalise the data across the different Nextdoor communities. We will aim to recruit approximately 1500 community dwellers aged 18 to 90 years across each country (Australia, UK, USA), with an overall estimate of 4500 participants across three countries. These recruitment targets are feasible given the number of users active within each country (at least 500,000 users).

The external organisation Nextdoor will be responsible for recruitment of participants and will invite users within each country without specific parameters. This is to ensure we recruit all kinds of users, including those who are high and low users of the program, and those who are from low to high socio-economic status. Potential participants will respond to advertisements embedded in the Nextdoor website platform that they are already a member of. Nextdoor will recruit via email, push notifications (website and app). If an individual is interested in participating, they will be directed to a Qualtrics survey containing a participant information statement and consent form. This Qualtrics survey is only accessible by Swinburne University of Technology. In this survey, participants will provide online consent to take part in Nextdoor KIND Challenge. Following consent being obtained, participants will complete a baseline survey and will be randomised into the KIND Challenge condition or a waitlist condition.

### Allocation and blinding

Simple randomization (1:1) will be used as the study is conducted entirely on online questionnaire software Qualtrics. Blinding is not possible in this RCT and there may be recruitment biases that may occur (e.g., those who choose to participate may already be more altruistic and more open to being engaged within research studies).

### Data collection and management

#### Data collection

Assessment data will be collected online via the Qualtrics survey platform using a digital case report form. Data will be extracted to a secure data file and stored on a secure network. Data is screened for duplicates and removed by the research assistant using categorisation function on Microsoft Excel. For each stage of data cleaning and analysis that is performed, a separate time-stamped computer file will be created and saved within an organised file system. To aid data quality, checks will include examination of recorded data for out-of-range values and data entry errors.

#### Data management

Data collected in this randomized control trial will be managed in accordance with the relevant research ethics board. All researchers will have to follow the relevant ethics procedures and protocols for managing and storing data. Restrictions to the data will be made such that only those listed as an author in this protocol, as well as the host institutes, will have access to the data. The host institutes access will be specific to audit and regulatory processes and will not be used for any purpose outside the scope of the trial registry.

### Statistical methods

All analyses will be conducted individually for each country to reflect differing responses to COVID-19 related social restrictions in place during the intervention. This means that there will be three separate randomised controlled studies. Initial screening will be conducted to check normality and score distribution (e.g., skew and kurtosis) on all outcome variables. Where data distributions fall outside of acceptable levels of normality, subsequent analysis will account for that using non-normality robust estimators (such as the Mplus estimator MLR; [57]). To ensure randomisation was successful, balance at baseline will be assessed between the trial and control group on all outcomes i.e., primary outcome loneliness, secondary outcome social isolation, and secondary neighbourhood relationship quality and contact outcomes (c) social cohesion and trust, (d) perception that their neighbourhood is improving, (e) importance around getting to know their neighbours, (f) supportive, aversive, or ambivalent neighbour network classification, (g) neighbourhood conflict, (h) number of neighbourhood contacts, and the secondary mental health outcomes, (i) depression, (j) social anxiety, (k) stress, (l) quality of life, and (m) positive affect. MANOVAs will be used for interval data and Chi square for nominal data; effect size differences will be reported.

To assess trial effects, ITT analysis will provide an unbiased estimate of the impact of the intervention [58] comparing participants assigned to the KIND Challenge with those in the control group. ITT includes every participant that is randomised and ignores adherence and compliance and anything that happens post randomisation. Thus, participants are analysed as randomised, reducing bias and with the purpose of ensuring groups differ only on the intervention being compared. ITT, therefore, represents real practical scenarios in which lack of adherence and compliance would naturally be encountered. ITT will be applied to H1–4. ITT, however, suffers from issues of non-compliance because participants assigned to the intervention may not engage with it and, thus, would bias and dilute impact of the intervention. Therefore, H7 aims to explore how compliance, adherence, and engagement with the KIND Challenge intervention moderate impact on outcomes; H8 will assess the impact of compliance on outcomes, using Complier Average Causal Effects (CACE).

### Outcomes analysis

An ITT analyses approach, using linear multiple regression modelling in Mplus 8.3, will be employed. A KIND Challenge intervention effect can be noted if the coefficients associated with the trial group variable are statistically significant and effect size recorded.

A model building approach will be used. Model 1 will include loneliness as the outcome variable, with explanatory co-variates gender, age group, baseline loneliness respectively. The target variable trial group (KIND Challenge versus control group) will be added with control group as the reference group (coded 0). Sensitivity analysis will be conducted to determine if effects are robust and are maintained once additional explanatory variables are controlled for.

Model 2 will build in additional secondary and mental health explanatory variables, e.g., baseline social isolation, depression, social anxiety, stress, quality of life, positive affect, given their known associations with the response variable.

Model 3 will build in additional community explanatory variables, e.g., baseline levels of Nextdoor platform activity (both active and passive use), baseline community engagement, Pre-KIND Challenge neighbourhood contact and previous kindness activity engagement, and neighbourhood relationship quality variables of (a) social cohesion and trust, (b) perception that their neighbourhood is improving, (c) higher importance around getting to know their neighbours, (d) feelings of ambivalence towards their neighbours, supportive, aversive, or ambivalent neighbour network classification, (e) neighbourhood conflict, and (f) number of neighbourhood contacts.

Model 4 will build in controlling for COVID-19 climate by asking respondents the number of government restrictions imposed (from a list of 13 types of restrictions).

### Secondary outcomes analysis

The above ITT analysis using linear multiple regression modelling in Mplus 8.3, will be repeated for the secondary outcome of social isolation (H2) and the neighbourhood relationship quality outcomes H3 (a) social cohesion and trust (measured using the Social Capital Scale) at post 4-week intervention. For outcomes (b) perception that their neighbourhood is improving (categorised at improving, stable or declining), and (d) supportive, aversive, or ambivalent neighbour network classification, because those are categorical data, we will use a multi-nominal regression. Outcomes (c) higher importance around getting to know their neighbours (high and low importance), (e) neighbourhood conflict (no neighbourhood conflict and instances of neighbourhood conflict), and (f) number of neighbourhood contacts (0–5 and 6+ neighbourhood contacts) are dichotomous categorical data so we will use a binominal regression to explore ITT effects. Similarly, for all mental health secondary outcomes at post 4-week intervention, H4 (a) depression (b) social anxiety, (c) stress, (d) quality of life, and (e) positive affect, measured using the PHQ-8, Mini-SPIN, PSS-4, EUROHIS-QOL-8, and PANAS-PA respectively. The same model building approach will be adopted as in H1.

To model whether effects are maintained for all outcomes (H5) in the participants assigned to the KIND Challenge group, a series of within-group ANCOVAs will be run. Differences in baseline (T1), post-intervention (T2), and one-month follow-up (T3) outcomes will be analysed for both primary and secondary outcomes. A model building approach will be taken controlling co-variates outlined above for H1–4. The sustainability of the intervention (H6) will be explored to determine if the participants assigned to the KIND Challenge group continue with acts of kindness. Both the frequency and duration of KIND acts completed in the one-month follow-up, and the level of engagement for each type of activity completed (i) emotional support, (ii) tangible support, (iii) informational support, (iv) belonging support, and (v) companionship support will be analysed. A series of within-group ANCOVAs will be run using the frequency and duration of KIND acts completed post 4-week intervention and one-month follow-up, to determine if engagement is sustained.

For feasibility, acceptability, and safety, we will present the descriptive statistics on these indicators (feasibility = < 40% drop out; acceptability more than 5 or higher on meaningful, safe, positive, and comfort ratings; and no reported conflicts because of doing the KIND challenge).

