Hypothesis 1 (H1): There will be a reduction in loneliness in participants assigned to the Nextdoor KIND Challenge groups compared to the waitlist control group post the 4-week intervention.Hypothesis 2 (H2): There will be a reduction in social isolation in participants assigned to the Nextdoor KIND Challenge groups compared to the waitlist control group post the 4-week intervention.Hypothesis 3 (H3): There will be an improvement in neighbourhood relationship quality and contact outcomes (a) social cohesion and trust, (b) perception that their neighbourhood is improving, (c) higher importance around getting to know their neighbours, (d) more likely to be classed as having a supportive neighbour network than not, (e) have lower neighbourhood conflict, and (f) increased number of neighbourhood contacts, in participants assigned to the Nextdoor KIND Challenge groups compared to the waitlist control group post the 4-week intervention.Hypothesis 4 (H4): There will be an improvement in mental health secondary outcomes, lower (a) depression and (b) social anxiety, (c) stress, and greater (d) quality of life, and (e) positive affect, in participants assigned to the Nextdoor KIND Challenge groups compared to the waitlist control group post the 4-week intervention.

While it is vital to investigate the impact of KIND Challenge post intervention, it is possible for impact on outcomes to be distal; that is indirect effects caused by changes in proximal outcomes. The KIND Challenge aims to reduce loneliness and social isolation, which may lead to later distal impact on other outcomes. Capturing impact at one-month follow-up after the completion of the KIND Challenge enables modelling the maintenance of intervention effects, i.e., are effects sustained at one-month or are sleeper effects present? In addition to understanding whether effects of the intervention are sustained, it is also important to know whether the intervention itself is sustainable. The KIND Challenge acts are positive, engaging, and feasible to the average individuals, and thus designed to be sustainable.
Hypothesis 5 (H5): The Nextdoor KIND Challenge effects noted in H1–4 above will be maintained at one-month follow-up for the participants randomly allocated to KIND Challenge group.Hypothesis 6 (H6): The KIND Challenge is sustainable, participants assigned to the KIND Challenge will continue engaging in acts of kindness at one-month follow-up.

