#### Social relationship index - Neighbourhood modified [39, 40]

The 3-item scale was modified from the Social Relationship Index (SRI) which measures both positivity and negativity in relationship ties which can indicate if one has supportive, ambivalent, or aversive ties [39, 40]. We ask participants how helpful, upsetting, and mixed/conflicted their feelings are towards their neighbours when needing advice, understanding, or a favour – rated on a Likert scale from 1 (not at all) to 6 (extremely). Based on these scores and using a threshold model classification, participants are then categorised to either having a supportive, aversive, or ambivalent neighbour relationship.

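### H3(d) is a two-category prediction (supportive or not), but the planned three-class multinomial regression yields two pairwise coefficients, neither of which tests it, and no rule says how they decide

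*Protocol article*

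**What the plan says.** - **Hypothesis** (Objectives, H3): KIND participants, compared with waitlist, will be "more likely to be classed as having a supportive neighbour network than not" after the four-week intervention.
- **Outcome** (Social relationship index – Neighbourhood modified): ratings of how helpful, upsetting and mixed or conflicted neighbours are go through a threshold model, and "participants are then categorised to either having a supportive, aversive, or ambivalent neighbour relationship".
- **Model** (Secondary outcomes analysis): for outcome "d) supportive, aversive, or ambivalent neighbour network classification, because those are categorical data, we will use a multi-nominal regression". The same paragraph gives outcomes (c), (e) and (f), which it treats as dichotomous, a binomial regression.
- **Decision rule** (Outcomes analysis): a KIND Challenge "intervention effect can be noted if the coefficients associated with the trial group variable are statistically significant". It is written for the loneliness regression. The secondary section extends the H1 model-building approach and offers no other rule.

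**The concern.** The hypothesis divides participants into two groups, while the model divides them into three and compares the classes in pairs. A three-class multinomial regression has two trial-group coefficients. With supportive as reference they compare ambivalent with supportive and aversive with supportive. With another class as reference, one of the two does not involve supportive at all. The coefficients can differ in size, significance or sign.

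Applied to this outcome, the stated rule could mean that either coefficient suffices, that both are needed, or that they are tested jointly. These readings have different error rates, and none of them is the H3(d) question. At stake is whether the trial can claim or reject H3(d) on a test of that prediction, with the reading fixed before the data are seen.

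**Working it through.** **Inputs from the protocol.** 1500 participants per country, alpha 0.05 and power 0.80 (Sample size); 1:1 allocation (Allocation and blinding), so about 750 per arm; drop-out below 40% as the feasibility limit (Feasibility), so 750 × 0.60 = 450 per arm as a low case.

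**Assumptions.** The protocol gives no class proportions for this outcome and no figure for H3(d) to reproduce. Class splits (supportive/ambivalent/aversive), a 7-point gain, two-sided tests and no covariate adjustment are assumed.

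**Check on the inputs.** The one stated design figure, an MDES of .14 for loneliness, follows from (t₀.₉₇₅ + t₀.₈₀) × √[(1 − R²)/(0.25 N)]. With N = 1500 and R² = .35² = .1225 this is 0.136, which rounds to .14.

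**Step 1: what the coefficients measure.** With supportive as reference and G the arm,

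P(supportive) = 1 / [1 + exp(a₁ + b₁G) + exp(a₂ + b₂G)].

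P(supportive) is the same in both arms when exp(a₁ + b₁) + exp(a₂ + b₂) = exp(a₁) + exp(a₂). That is one condition on b₁ and b₂ together. It can hold with neither equal to zero, so testing b₁ or b₂ separately does not test H3(d).

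**Step 2: supportive unchanged.** Waitlist 50/30/20, KIND 50/36/14.
- Supportive versus not: OR = 1.00.
- Supportive versus ambivalent: OR = (50/36)/(50/30) = 0.83. SE = √(1/375 + 1/270 + 1/375 + 1/225) = 0.116; power 0.35.
- Supportive versus aversive: OR = (50/14)/(50/20) = 1.43. SE = √(1/375 + 1/105 + 1/375 + 1/150) = 0.147; power 0.68.

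In 100,000 simulated trials at 750 per arm, at least one of these two coefficients is significant in 84% (63% at 450 per arm). In 68% one is significant in the direction favouring KIND, and in about 20% the two are significant in opposite directions. The joint 2-df test rejects in 88%. The binary test stays at 5%.

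**Step 3: no effect at all, 750 per arm.** Splits 50/40/10, 60/30/10, 70/20/10 and 50/30/20.

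| Reading | Type I error |
|---|---|
| Either coefficient | 9.3–9.7% |
| Both coefficients | 0.3–0.5% |
| Supportive versus not | 4.7–5.3% |

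**Step 4: a true 7-point gain in supportive, 750 per arm.** The other two classes shrink in proportion.

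| Control → KIND | Binary | Joint 2-df | Both |
|---|---|---|---|
| 60/30/10 → 67/24.75/8.25 | 80% | 71% | 30% |
| 50/40/10 → 57/34.4/8.6 | 78% | 68% | 27% |
| 50/30/20 → 57/25.8/17.2 | 78% | 68% | 38% |

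Here the either reading matches the binary test (79–80%); its cost is the error rate in steps 2 and 3. At 450 per arm the binary test has 55–59% power, the joint test 45–48% and the both reading 14–20%.

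**The case against.** **The model contains the answer.** Multinomial regression is a standard choice for three unordered classes, and P(supportive) by arm can be computed from the fit. It also keeps the ambivalent/aversive distinction, which bears on the stated objective of more positivity and less negativity towards neighbours. This stands: the model need not be discarded. The article, however, names no such contrast and instead points to significance of the coefficients, which answers a different question.

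**The rule was written for one coefficient.** It follows the linear regression for loneliness, and its plural may simply cover Models 1 to 4. This also stands. A reader might infer that the plan adopts an either-coefficient rule with about 9–10% false positives; the documents do not say so. The error rates above show what each reading would cost.

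**This is detail for a SAP.** Reference class and output format would be. A stated hypothesis, model and rule that do not fit together are a mismatch within the article.

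**Weak ties.** A reader might also infer that someone who rates neighbours low on both helpful and upsetting falls outside the three classes and is dropped, biasing the comparison. The documents do not support this. They say participants are "categorised to either having a supportive, aversive, or ambivalent neighbour relationship", a third mixed or conflicted item enters the scoring, and no cut-points are printed. The thresholds may place such a person in one of the classes, and no exclusion is stated.

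**Conclusion.** The mismatch is real. H3(d) is a supportive-versus-not prediction; the planned model's coefficients are pairwise, and the stated rule does not say how two of them decide it. The most telling case is step 2: followed as written, the plan could report an effect on this outcome when the proportion classed as supportive has not moved.

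The sizes are illustrative, because class proportions and gain are assumed and the planned covariates are left out. That neither coefficient is the H3(d) contrast does not depend on those assumptions. No loss or misclassification of participants with weak ties is shown. H3(d) is one of six components of a secondary hypothesis, so this should be corrected but does not touch the primary outcome, the sample size or data collection.

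**What to change.** Make the H3(d) test a logistic regression of supportive (1) versus all other classified participants (0), with the trial-group term and the same Model 1–4 covariates. This is the binomial approach the same paragraph already uses for (c), (e) and (f). One prespecified contrast between arms in the marginal probability of supportive, taken from the multinomial model, would serve the same purpose. State that this single test decides H3(d), and report the pairwise multinomial coefficients as descriptive.

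The cost is a change of wording using data already collected. The small downside is that the split between ambivalent and aversive is no longer formally tested.
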